**2.4 Clinical exams**

(1) auto-refractor

(2) non-contact tonometer

(3) phoropter

(4) corneal topography（Pentacam, Toplyzer）

(5) Wavefront sensor (iTrace)

(6) Visante-OCT

(7) slit-lamp microscope

(8) A-scan ultrasound pachymetry

**3 Study design**

**3.1 Subjects：**recruit subjects as protocol.

**3.2.1 Inclusion criteria**

Normal group：

1. no eye surgery,trauma; 2. no other eye dieases: glaucoma,retina disease; 3. no limiting image quality diseases: severe dry eye, eyelid calculi, conjunctivitis and pterygium; 4. quit contact lens: RGP > 4 weeks, SCL > 2 week; 5. no fixing problem.

Refractive surgery group：

1. age：≥18yrs；2. refractive status：sphere：-1.00~-12.00 D, cylinder：≤ -6.00 D；3. refractive status maintain stable in recent 2 yrs，progressive ≤ 0.50 D per year.

Keratoconus group：

Suspected and diagnosed Keratoconus patients ：1. history of myopia and astigmatism；2. corrected visual acuity <1.0；3. abnormal corneal topography：central anterior corneal curvature >47D, curvature difference of inferior 3mm and superior 3mm of anterior cornea IS>3D, binocular curvature difference >1D；4.slit lamp observe one of the signs：corneal stromal thinning, corneal cone, Fleischer’s ring, Vogt stria, cornea scar.

**3.2.2 Exclusion criteria**

1. eye conditions not available; 2. active inflammation; 3.retina dieases; 4. system disease affect eyes; 5. other disease affect wound healing; 6. carrer limiting.

**3.3 Study procedures**

**3.3.1 Clinical screening**

Normal group：

Clinical exams：uncorrected visual acuity, computer optometry, non-contact tonometer, subjective refraction, corneal topography (Pentacam, Toplyzer), pupil size, slit lamp imaging, Visante-OCT, mydriasis test, A-scan ultrasound pachymetry, axial lengths, lacrimal passage check.

Slit lamp imaging：capture central cornea images with diffused light, narrow band light, wide band light.

Refractive surgery group：

Pre-operation exams：uncorrected visual acuity, computer optometry, non-contact tonometer, subjective refraction, corneal topography (Pentacam, Toplyzer), pupil size, slit lamp imaging, Visante-OCT, mydriasis test, A-scan ultrasound pachymetry, axial lengths, lacrimal passage check.

Slit lamp imaging：capture central cornea images with diffused light, narrow band light, wide band light.

Keratoconus group：

Clinical exams：uncorrected visual acuity, computer optometry, subjective refraction, corneal topography (Pentacam, Toplyzer), slit lamp imaging, Visante-OCT, mydriasis test, A-scan ultrasound pachymetry, axial lengths, lacrimal passage check.

Slit lamp imaging：capture central cornea images with diffused light, narrow band light, wide band light.

**3.3.2 Formal study**

**（1）visiting spots：**Pre, post 1 day, 1week, 2 weeks, 1month, 3months.

**（2）OCT scanning：**according torandom number table, select one eye.

**A. UL-OCT：**run: C:\OCT\combined_x-y\OCT-T34-Combined_1.vi

1.Obtain OCT images as following：

**1）Central 3D radial scanning：**calibrated scan width 18.291mm.Scanning setting：“X/Y scan width” set as 15, “line rate” set as 24000 k/A-line，“scan pattern” set as 2048×324 mm radial.

[figure not shown]

**2）Horizontal 2D scanning：**calibrated scan width 12.139 mm. Scanning setting：“X/Y scan width” set as 10, “line rate” set as 24000 k/A-line，“scan pattern” set as 2048×324 mm.

[figure not shown]

**3）Vertical 2D scanning：**calibrated scan width 12. 248 mm. Scanning setting：“X/Y scan width” set as 10, “line rate” set as 24000 k/A-line，“scan pattern” set as 2048×324 mm.

[figure not shown]

**2. Naming rules：** NO1_XX_S_1M_OD_2D_X10_1

**3. Data saving：** E:\LASIK_OCT\UL\Time\Subject

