## 1 Study instructions

- 1. **Backgrounds**

The excimer laser served as a surgical tool was first introduced into ophthalmology and refractive surgery almost 30 years ago. Compared with photorefractive keratectomy (PRK), laser situ keratomileusis (LASIK）reduce postoperative pain, haze and accelerate visual recovery. LASIK is nowadays the most popular corneal refractive surgery around world. With the development of femtosecond laser (FEMTO), flap creation methods were improved at the same time. Sub-Bowman’s keratomileusis (SBK) combines the advantages of PRK and LASIK, creates thinner flaps in accurate and precise ways. Thus, SBK improved the efficacy, tolerability, and safety of refractive surgery.

Keratoconus is a bilateral asymmetry ectasia disease, which is characteristic with cornea thinning. However, when patients were in early stage, there were no obvious clinical signs and symptoms. Even the most sensitive corneal topography could not diagnosis. The only complain was reduced visual acuity. If the preoperative screening missed such kind of patients, cornea refractive surgery might lead to keratectasia. Thus, it is important to diagnose these subclinical patients in the stage of cornea thickness thinning.

Optical coherence tomograghy (OCT) relays on the principles of low-coherence interferometry to differentiate corneal sublayer structures. Anterior segment OCT advantaged in high acquisition speed, high axial resolution and non-invasive contact. With improved imaging technologies and surgical skills, it is promising that the diagnosis and treatment method will benefit more patients and scientific researchers.

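### The random one-eye rule is not tied to the eye that meets the keratoconus criteria, nor to the eye that is staged

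*Protocol*

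**What the plan says.** Section 3.3.2 (Formal study), under OCT scanning, states the rule: "according torandom number table, select one eye". The section names no group, exempts none, and does not make the draw depend on eligibility. It also holds the only acquisition instructions for the two study OCT devices.

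The background in section 1 states: "Keratoconus is a bilateral asymmetry ectasia disease, which is characteristic with cornea thinning".

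Section 3.2.1 admits suspected as well as diagnosed keratoconus patients. Its criteria include "corrected visual acuity <1.0", "central anterior corneal curvature >47D", "curvature difference of inferior 3mm and superior 3mm of anterior cornea IS>3D", "binocular curvature difference >1D" and a slit-lamp item that begins "slit lamp observe one of the signs". It does not say whether one eye or both must meet them.

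Aim B (section 1.2) relates corneal thickness to keratoconus stage. Section 1.3 describes stage as an attribute of the patient. Section 3.6 lists the t-test, linear regression and Pearson's correlation.

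**The concern.** Drawing one eye at random is a sound way to get one independent observation per person when either eye could represent that person. In an asymmetric disease the two eyes are not interchangeable. Patients enter on findings that may belong to one eye only, and nothing ties the draw to that eye.

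Two errors can follow. A fellow eye that meets none of the eye-level criteria can enter the data as a keratoconus eye. And if one stage is recorded per patient, thickness from one eye can be set against a stage determined by the other. The second error bears directly on Aim B.

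A statistical analysis plan could specify eye-level staging, but it could not repair the choice of eye. That choice is made at acquisition, and an eye never scanned with the study OCT has no study thickness to analyse.

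**Working it through.** **1. Figure to reproduce.** There is none. The protocol states no sample size, power, significance level or effect size that depends on the choice of eye. The check is a reading of the text plus one simple formula.

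**2. Unit of each keratoconus criterion in section 3.2.1.**
- Corrected acuity below 1.0: one eye.
- Central anterior curvature above 47 D: one eye.
- Inferior-superior difference above 3 D: one eye.
- At least one slit-lamp sign: one eye.
- History of myopia and astigmatism: patient.
- Curvature difference above 1 D between the eyes: the pair of eyes.

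Four of the six items are properties of a single eye. The unit admitted is the patient, the unit scanned is one eye drawn at random, and the unit staged reads as the patient. No section links these three.

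**3. Non-qualifying eyes.** Let u be the share of keratoconus patients with exactly one qualifying eye. The documents do not give u, so the values below are assumptions. An unrestricted draw takes the other eye with probability 1/2:

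share of scanned eyes that do not qualify = u × 1/2

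| u (assumed) | u/2 |
|---|---|
| 0 | 0 |
| 0.10 | 0.05 |
| 0.20 | 0.10 |
| 0.30 | 0.15 |
| 0.50 | 0.25 |

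The logical limits are 0 (both eyes always qualify) and 1/2 (never more than one does).

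**4. Stage and thickness from different eyes.** Let v be the share of patients whose eyes differ in stage, also not given. If one stage per patient is recorded from one eye, the draw takes the other eye in v/2 of patients. This can happen even when both eyes qualify, so u = 0 does not rule it out. It overlaps with step 3, so the two shares should not be added. If the recorded stage came from the worse eye, a less affected cornea would be entered under a later stage. Since the protocol describes the disease as one of thinning, that pulls the fitted slope of thickness on stage towards zero. If each scanned eye carries its own stage, this error is absent whatever v is.

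**5. After the correction.** If the draw is limited to qualifying eyes, the share in step 3 is 0 by construction. If the scanned eye's own stage is used, the share in step 4 is 0.

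**The case against.** The strongest reply is that section 3.3.2 was written around the surgery cohort. Its visits are pre-operative and post-operative, and its data folders carry a LASIK label. On that view the protocol is silent on keratoconus eyes rather than wrong about them. This stands in part: that the rule governs every group is a reading of unrestricted text. But Aim B needs keratoconus scans and no other scanning instruction exists. If the rule does not apply, there is no rule for choosing the eye, and the same sentence has to be written.

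Second, a less affected fellow eye may be legitimate data. The background stresses subclinical disease, suspected cases are admitted, and Aim B wants a range of stages. This also stands, and an eye labelled with its own stage does not distort the relationship. A random draw, however, neither seeks such eyes nor labels them. Nor does the protocol fix how stage is recorded; the patient-level wording in section 1.3 may be loose phrasing.

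Several stronger readings are tempting but not supported:
- **That every keratoconus patient must differ by more than 1 D between eyes.** The three topographic items are listed with commas and neither an *and* nor an *or*, so they may be alternatives. Even if the item were mandatory, eyes at 52 D and 49 D differ by 3 D and both exceed 47 D.
- **That the design loses half its data by scanning one eye.** The number of independent patients is unchanged, and fellow eyes are correlated.
- **That a keratoconus-normal difference is attenuated by some stated percentage.** Aim B does not state that contrast, u is unknown, and the percentage would require an unaffected fellow eye in a disease that the protocol calls bilateral.

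**Conclusion.** The point holds as a defect in a stated rule. As written, the eye draw is not limited to eyes that meet the keratoconus criteria, and the stage used for Aim B is not tied to the scanned eye. Following the text can misclassify eyes and can set thickness against the wrong eye's stage.

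The size is u/2 for non-qualifying eyes, with u unknown and zero effect if both eyes always qualify. Misalignment of stage and thickness arises only if stage is recorded per patient and the eyes differ in stage. The documents support no narrower figure. The conclusion rests on section 3.3.2 applying to the keratoconus group, which is the natural reading because it is the only scanning instruction. The single-eye rule itself is not at fault for the normal and refractive surgery groups. The change should be made because it is cheap and because an unscanned eye cannot be recovered later.

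**What to change.** Amend sections 3.2.1 and 3.3.2 for the keratoconus group:
- Apply the eye-level entry criteria and the stage to each eye separately. Criteria that concern the patient or the pair of eyes stay at patient level.
- Draw the study eye only among eyes that qualify, using the random number table only when both do.
- In the Aim B analysis, relate thickness to the scanned eye's own stage.
- If less affected fellow eyes are wanted as subclinical data, say so, and record and label them as such.

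Keep the random single-eye rule for the normal and refractive surgery groups.

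The cost is protocol wording and an eye-level stage field on the record form, with no extra imaging. The one downside is that fewer mild fellow eyes are sampled unless they are deliberately included.

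Scanning both eyes, with an analysis that allows for the correlation within a patient, is optional. It would have to fit the half-hour limit in section 4.1. Section 3.3.2 lists 3 + 7 = 10 acquisitions per eye across the two devices, so both eyes means 20 before any repeats for image quality.

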**4. Notice：**

(1) Using apex to adjust cornea vertex registration and relocation;

(2) Keep iris plane balanced;

(3) Check the image quality after each acquisition. Reacquire if the image quality is not good enough.

(4) Open the eyelid wide to avoid eye lash artifacts.

(5) Check 3D scanning image quality. Require if the reconstruction is not smooth.

**B． UHR-OCT：**run: C:\OCT\combined_x-y\OCT-T34-Combined_1.vi

1. Obtain OCT images as following：

**1）Central horizontal 2D scanning：**calibrated scan width 8.425 mm. Scanning setting：“X/Y scan width” set as 7, “line rate” set as 24000 k/A-line，“scan pattern” set as 2048×326 mm.

[figure not shown]

**2）Nasal horizontal 2D scanning：**calibrated scan width 8.425 mm. Scanning setting as “1）Central horizontal 2D scanning”.

**3）Temporal horizontal 2D scanning:** calibrated scan width 8.425 mm. Scanning setting as “1）Central horizontal 2D scanning”.

**4）Central vertical 2D scanning：**calibrated scan width 8.418 mm. Scanning setting：“X/Y scan width” set as 7, “line rate” set as 24000 k/A-line，“scan pattern” set as 2048×326 mm.

[figure not shown]

**5）Superior vertical 2D scanning：**calibrated scan width 8.418 mm. Scanning setting as “1）Central vertical 2D scanning”.

**6）Inferior vertical 2D scanning：**calibrated scan width 8.418 mm. Scanning setting as “1）Central vertical 2D scanning”.

**7）Central 3D radial scanning：**calibrated scan width 8.418 mm. Scanning setting：“X/Y scan width” set as 10.5, “line rate” set as 24000 k/A-line，“scan pattern” set as 2048×324 mm radial.

[figure not shown]

**2. Naming rules：** NO1_XX_S_1M_OD_N_2D_X10_1

**3. Data saving:**  E:\LASIK_OCT\UHR\Time\Subject

**4. Notice：**

(1) Using apex to adjust cornea vertex registration and relocation;

(2) Keep iris plane balanced;

(3) Check the image quality after each acquisition. Reacquire if the image quality is not good enough.

(4) Open the eyelid wide to avoid eye lash artifacts.

(5) Check 3D scanning image quality. Require if the reconstruction is not smooth.

**3.4 OCT imaging processing:**

UL-OCT: using custom developed automated software to reconstruct cornea.

UHR-OCT: using custom developed automated software to obtain thicknesses of each corneal sublayers.

Imaging processing: (1) raw images; (2) manual measurements (J-OCT): interfaces and boundaries of each sublayer; (3) automated Matlab code: detailed measurement results of all corneal layers.

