**1.2 Aims**

A. Using OCT to obtain corneal images before LASIK, post LASIK 1 day, 1 week, 2 weeks, 1 month. Compare the differences between two flap creation methods.

B. Observe the cornea images acquired from keratoconus patients in different stages. Analysis thickness data and the relationship between the thickness and stage.

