**1.3** **Hypothesis**

During the observation of following-ups, OCT images might capture the changes before and after LASIK. The relationship between flap creation methods, ablation depth and corneal thickness might be captured. After LASIK, cornea edema might appear on the OCT images. As the longer observation time after surgery, cornea edema might reduce. Slit lamp will be used during following-ups and assist to image cornea. OCT will image the interfaces and boundaries of corneal sublayers and flaps.

At the same time, clinical exam results will be documented. Combined with OCT images, correlation between refractive regression, corneal curvature and corneal edema will be studied.

Keratoconus patients will be examed by clinical instruments. Patients of different stages will be included. OCT images will analysis combined with clinical data to study the relationship between the corneal thickness and disease courses.

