**5 Study records**

Each subject will be documented separately. Researcher should keep detailed and private information for each subject. The reports of each visiting will be maintained and concluded after each study time spot. Researcher should check the study results and sign the names and date with black pen formally. If the information need to be corrected, single horizontal line should be used to mark over the records and sign with the researcher’s name and date. The corrected part should be maintained recognizable. If the records are not able to be distinguish, “*” should be marked with commons. The OCT image results of each subject will be recorded in DVD discs and named after naming rules. The results may be used to compare with clinical results when necessary. All the records will be well kept at least 5 years.

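### Hand-placed OCT boundaries are not protected from a reader who can see visit and subject, which may bias comparisons among post-operative visits wherever manual values are used

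*Protocol*

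**What the plan says.** Protocol section 3.4 (OCT imaging processing) describes two routes to a measurement. For UHR-OCT it plans "using custom developed automated software to obtain thicknesses of each corneal sublayers". It then lists three processing steps: raw images, then "manual measurements (J-OCT): interfaces and boundaries of each sublayer", then "automated Matlab code: detailed measurement results of all corneal layers". It does not say which values enter the analysis, or whether the manual boundaries are an input to the code, a check on it, or a result in their own right.

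Section 3.3.2 (Formal study) fixes the labels. The UL-OCT file name template is "NO1_XX_S_1M_OD_2D_X10_1" and the UHR-OCT template is "NO1_XX_S_1M_OD_N_2D_X10_1". Each carries a number, what reads as a visit code (1M) and an eye code. The storage paths for both instruments end in a time folder and, inside it, a subject folder. Section 5 carries the names into the archive: "The OCT image results of each subject will be recorded in DVD discs and named after naming rules".

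On expectation, section 1.3 says: "As the longer observation time after surgery, cornea edema might reduce". Section 1.2, aim A, adds: "Compare the differences between two flap creation methods". The visits in section 3.3.2 are before surgery and 1 day, 1 week, 2 weeks, 1 month and 3 months after it.

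**The concern.** Placing a layer boundary by hand is a judgement. A reader who knows that an image is from day 1 rather than month 1, who can find the same subject's earlier readings, and who expects swelling to subside may place boundaries slightly further apart at early visits and closer together at late ones. Such a shift is systematic. It enters the visit contrast as bias, and more eyes do not average it away: the standard error shrinks around the wrong value. Nor can a later analysis remove it once the boundaries have been read with the labels in view. What is at stake is whether a decline in manually measured layer or flap thickness after surgery can be attributed to the cornea rather than to the reader.

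**Working it through.** The protocol states no sample size, SD, significance level, effect size or reader error, so there is no planned figure to reproduce. The check is mainly a comparison of sections.

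**1. Is there a manual step?** Yes. It is step 2 of the processing list in 3.4.

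**2. Do the labels show visit and subject?** Yes. The folder levels in 3.3.2 are time and subject, so this can be seen without the naming legend in section 7.1, whose figures are not shown. The example name also contains 1M.

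**3. Do the labels show the flap method?** Not in the readable text. Two fields of the template (XX and S) are unexplained there and cannot be assumed to be a method code. A reader would have to link the subject to the operation, know it from the clinic, or infer it from the image.

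**4. Is there an expected direction?** Over time, yes (1.3). Between the two flap methods, none is stated.

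**5. Does the manual step reach the analysed data?** The protocol leaves this open.

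| Possible role of the manual boundaries | Can the reader bias the results? |
|---|---|
| They are the analysed values | Yes |
| They seed the Matlab code or correct its output | Yes, through the code |
| They only check the software and change nothing | No |

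**6. Which outcomes are exposed?** Section 2.1 assigns corneal thickness to UL-OCT, which 3.4 reconstructs automatically. Section 2.2 assigns epithelium, Bowman's layer and flaps to UHR-OCT. The manual step concerns sublayers, so the exposure is clearest for sublayer and flap measurements. The protocol does not define its edema measure. If that is total thickness from UL-OCT, it need not pass through a reader.

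**7. Which contrasts are exposed?** The flap itself is likely to separate pre- from post-operative images whatever the label says. It does not by itself tell the reader which of the five post-operative visits is on screen, or what was measured before. The label does.

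**Illustration only (all inputs assumed).** Take a paired t-test between two post-operative visits at a two-sided 5% level, 30 eyes, no true change, and a consistent reading shift b. The non-centrality is b / (SD of difference / √30), with 29 degrees of freedom.

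| Assumed shift b | Assumed SD of difference | Non-centrality | False-positive rate |
|---|---|---|---|
| 1 µm | 10 µm | 1 / (10/5.477) = 0.55 | 8.3% |
| 1 µm | 5 µm | 1 / (5/5.477) = 1.10 | 18.5% |
| 3 µm | 10 µm | 3 / (10/5.477) = 1.64 | 35.5% |
| 3 µm | 5 µm | 3 / (5/5.477) = 3.29 | 88.8% |

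The only anchor in the documents is the UHR-OCT axial resolution of about 3.0 µm (2.2). That is a property of the instrument and not an estimate of reader bias. The table shows how sensitive a visit contrast would be to such a shift; it does not predict that one will occur.

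**The case against.** The strongest reply is that 3.4 assigns UHR-OCT thicknesses to automated software and ends in automated output, so the manual step may never touch the analysed data. That stands as a condition on the point: if manual boundaries only verify the software, there is no bias to remove. But the protocol does not say so, and it lists manual measurement of every sublayer.

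A second reply is that the naming rules serve capture and storage, where traceable labels are needed, and that masking could be set out in a reading manual or the SAP. The first half is right, and the labels should stay on the stored originals. On the second, this protocol specifies image handling down to the folder path and moves from labelled files to manual measurement with no step between. That the reader opens files under those names is an inference, though the natural one. A SAP could say which values are analysed, but it cannot undo readings already made with the labels in view.

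Two stronger readings are tempting and are not supported. A reader might infer that the file names bias the flap-method comparison. The readable templates show no method, no direction between methods is stated, and a shift driven by visit alone would move both methods alike at that visit and cancel in their difference. Any effect there is indirect, through the subject's identity or the look of the flap. A reader might also infer that the results will be biased by a known amount. The documents give nothing from which to derive one.

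**Conclusion.** The point holds as a conditional risk of bias and not as a demonstrated error. It rests on three assumptions: that manual boundaries are analysed, seed the code or correct its output; that the reader works from files labelled as the protocol prescribes; and that knowing the visit or earlier values affects boundary placement. Under these, comparisons of manually measured sublayers and flaps among the visits from 1 day to 3 months may drift towards the stated expectation. The size is unknown. The point is best treated as a cheap improvement, justified by its low cost and by the difficulty of repair after unmasked reading.

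**What to change.** In section 3.4:

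- State whether manual or automated values are analysed, and whether manual boundaries feed or correct the Matlab code.
- Before any manual J-OCT measurement or manual correction of automated boundaries, have a script copy the images under random codes without subject or visit. Leave the originals under their present names.
- Present the copies in shuffled order across subjects and visits.
- Join the key to the measurements only after the boundaries are locked.

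The cost is a short script and one linking step, with no extra reader, visit or patient burden. The limit should be stated openly: masking remains partial for pre- versus post-operative status and for flap method, because the image itself may reveal both. The main gain is among the post-operative visits.
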